#### 2.9.2. Primary Outcome: Total Dyspepsia Symptom Scale (TDS)

The TDS questionnaire evaluates eight items consisting of postprandial fullness/bloating, early satiety, epigastric pain and burning, nausea, vomiting, belching, and other dyspeptic symptoms on a 4-point Likert scale (0: none, 1: mild/weak, 2: moderate/average, and 3: severe) [11]. A higher overall score, obtained by adding up the points for each item, indicates more severe symptoms related to indigestion. The TDS has been used as a primary outcome in a number of clinical trials related to FD [11,19,22]. Therefore, the TDS will be measured at all visits except the screening visit. The degree of improvement in the TDS score during the trial period will be calculated using the following formula: $$\mathrm{Improvement}\;\mathrm{in}\;\mathrm{TDS}\;\left(\%\right)=\frac{TDS\;at\;baseline-TDS\;at\;N\;th\;week}{TDS\;at\;baseline}\times 100$$

The therapeutic effects will be classified as significant (≥75%), moderate (≥50%), mild (≥25%), and none (<25%) according to the improvement rate.

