### 2.11. Statistical Analysis

A statistician independent of the trial procedure and assessment will conduct statistical analysis using SAS^®^ Version 9.4 software (SAS Institute Inc., Cary, NC, USA). In principle, for effectiveness analysis, a full analysis set of all randomly assigned participants who are evaluated at least once after receiving a prescription of investigational products at least once will be conducted, according to intention-to-treat analysis. If necessary, per-protocol set (PPS) analysis will be performed, including participants who have completed the entire process of the clinical trial and have no significant violations affecting the test results. Participants with less than 70% compliance with the investigational product, taking prohibited drugs for the treatment and management of diseases other than gastrointestinal disease under the judgment of investigators, or experiencing events that can cause digestive symptoms such as sudden stress during the clinical trial period, will be excluded from the PPS analysis. Safety analysis will include all data obtained from participants who have taken at least one investigational product in the YGJ and PWS groups and all participants in the usual care group.

The demographic characteristics of participants will be summarized by group. Continuous data will be presented as mean and 95% confidence intervals (CIs), whereas dichotomous data will be displayed as frequency and percentage. The primary outcome of this study is the difference in the TDS score at week 6 between the YGJ and usual care groups (Hypothesis 1).

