**Hypothesis** **1.**
*[*

$H_{0}\;:\;\mu_{1}=\mu_{2},\;H_{1}\;:\;\mu_{1}\neq \mu_{2}$

*]*

*-*

$\mu_{1}$

*: Change in TDS score of the YGJ group at week 6*

*-*

$\mu_{2}$

*: Change in TDS score of the usual care group at week 6*

A two-sided test with a significance level of 5% will be conducted using a mixed-effect model repeated measure (MMRM) with participants as the random factor and the treatment group and time of visit as the fixed factors. If necessary, analyses will be performed by setting variables showing statistically significant differences in demographic characteristics or variables that can affect dyspepsia as the fixed factors. The second purpose of this study is to evaluate the noninferiority of YGJ compared to that of PWS (Hypothesis 3). Consequently, the noninferiority margin (*M*) will first be defined based on the results of the effect evaluation of PWS compared to usual care at week 6 (Hypothesis 2), and the analysis method will be the same as that of Hypothesis 1.

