**Hypothesis** **3.**
*[*

$H_{0}\;:\;\mu_{3}-\mu_{1}>M,\;H_{1}\;:\;\mu_{3}-\mu_{1}\;\leq M$

*]*

*-*

$\mu_{1}$

*: Change in TDS score of the YGJ group at week 6*

*-*

$\mu_{3}$

*: Change in TDS score of the PWS group at week 6*

To evaluate the noninferiority of YGJ compared to PWS, Hypothesis 3 will be tested in the same way as Hypothesis 1. However, since the noninferiority test is a single test, the significance level will be set to 2.5%, and the noninferiority margin will be defined as the lower limit of the 95% CI of Hypothesis 2. The multiple test problem will be solved using the fixed sequence method [29]. In other words, if the statistical test result for Hypothesis 1 is significant, the test for Hypothesis 2 will be performed, and if the statistical test result for Hypothesis 1 is not significant, the test for Hypothesis 2 and Hypothesis 3 will not be performed. If the statistical test result for Hypothesis 1 is significant and the test for Hypothesis 2 is performed, and if the statistical test result for Hypothesis 2 is significant, the test for Hypothesis 3 will be performed. If the statistical test result is not significant, the test for Hypothesis 3 will not be performed. If possible, subgroup analysis will be performed by categorizing the participants’ baseline characteristics, including age (65 years old or older/under), Rome IV subtype (EPS, PDS, and overlap), type of FD pattern identification (according to the standard tool for pattern identification of FD [21]: spleen–stomach deficiency and cold, spleen deficiency with qi stagnation, liver–stomach disharmony, cold–heat complex, spleen–stomach dampness and heat, and dietary retention and stagnation), deficiency and excess pattern identification, and the presence or absence of *Helicobacter pylori* infection and spleen qi deficiency syndrome (cut off score: 43.18 points in SQDQ [27]). In addition, we will combine the results of the YGJ and PWS groups corresponding to herbal medicine and compare them with the usual care control group.

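### As written, the primary mixed model has no group-by-visit term and no named week-6 contrast, so it gives one group effect pooled over unnamed visits, not the week-6 difference that Hypotheses 1 to 3 concern

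*Protocol article*

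**What the plan says.** Section 2.11 sets the target: "The primary outcome of this study is the difference in the TDS score at week 6 between the YGJ and usual care groups". The parameters of the hypotheses repeat the time point. The first is "Change in TDS score of the YGJ group at week 6", and those for usual care and Pyeongwi-san (PWS) are defined in parallel. Section 2.10 sizes the trial on a difference of 2.70 in TDS change after 6 weeks.

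The model for Hypothesis 1 is a mixed-effect model for repeated measures "with participants as the random factor and the treatment group and time of visit as the fixed factors". The text also allows, if needed, for including "variables showing statistically significant differences in demographic characteristics or variables that can affect dyspepsia as the fixed factors". These are covariates; an interaction is not among them.

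The same model is carried forward. For Hypothesis 2, "the analysis method will be the same as that of Hypothesis 1". Likewise, "Hypothesis 3 will be tested in the same way as Hypothesis 1". And "the noninferiority margin will be defined as the lower limit of the 95% CI of Hypothesis 2".

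On data collection, section 2.9.2 says that "the TDS will be measured at all visits except the screening visit", which by Table 1 means weeks 0, 3, 6, 9 and 24. Treatment ends at week 6 (section 2.1). Section 2.12 describes the week-24 telephone TDS as collected for the economic evaluation, after the 9-week effectiveness and safety trial. No section says which visits enter the model, or whether baseline is a response or a covariate.

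**The concern.** A repeated-measures model with main effects of group and visit has one coefficient per group comparison. It forces the treatment difference to be the same at every visit that it includes, so the resulting test concerns that common difference and not the difference at week 6.

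A constant effect cannot be taken for granted here. Week 3 is halfway through treatment, and weeks 9 and 24 fall 3 and 18 weeks after it ends. If the effect builds up and then fades, the pooled coefficient understates the week-6 difference.

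The consequence is not confined to one test. Hypothesis 1 opens the fixed sequence. Hypothesis 2 uses the same model and its confidence limit becomes the noninferiority margin. Hypothesis 3 is then judged against that margin with the same model. Fitted literally, none of the three would address the time point in its own definition.

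**Working it through.** **Inputs from the documents (section 2.10; two-sided level from section 2.11):** week-6 difference 2.70, SD 3.65, two-sided 5% level, 80% power, 2:1 allocation, 44 and 22 evaluable.

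**Assumptions, not in the documents:** the effect at visits other than week 6; the same SD at each visit; between-visit correlation ρ of 0.5 to 0.7; complete data.

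**1. Reproduce the planned sample size.** Usual care n = (1 + 1/2) × (1.96 + 0.8416)² × 3.65² / 2.70² = 21.5, so 22, and YGJ has 2 × 22 = 44. This matches the plan. The week-6 standard error is 3.65 × √(1/22 + 1/44) = 0.953. Power is Φ(2.70/0.953 − 1.96) = 81%. The sample size is therefore built on the week-6 difference alone.

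**2. What the additive model estimates.** With a random participant effect and complete data, the group coefficient is the plain mean of the visit-specific differences over the T modelled visits. Its standard error is 0.953 × √((1 + (T − 1)ρ)/T):
- T = 4: 0.75 at ρ = 0.5 and 0.84 at ρ = 0.7.
- T = 3: 0.78 and 0.85.
- T = 2: 0.83 and 0.88.

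**3. Results**, with power = Φ(pooled effect / SE − 1.96):

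| Assumed effects | Visits modelled | Pooled effect | Power, ρ = 0.7 to 0.5 |
|---|---|---|---|
| 1.35, 2.70, 1.35, 0 | 3, 6, 9, 24 | 5.40/4 = 1.35 | 36-43% |
| 1.35, 2.70, 1.35 | 3, 6, 9 | 5.40/3 = 1.80 | 56-64% |
| 1.35, 2.70 | 3, 6 | 4.05/2 = 2.03 | 64-69% |
| 2.0, 2.7, 2.0, 1.0 | 3, 6, 9, 24 | 7.7/4 = 1.93 | 63-72% |
| constant 2.70 | 3, 6, 9, 24 | 2.70 | 90-95% |

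If week 0 were also a response, with no difference at that visit, a constant 2.70 would pool to 10.8/5 = 2.16. The first pattern would pool to 5.40/5 = 1.08.

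**4. Simulation check.** In 100 simulated trials with 44 against 22, ρ = 0.5 and true effects of 1.35, 2.70, 1.35 and 0, the additive model gave a mean estimate of 1.37 (SE 0.75). The model with group-by-visit gave a mean week-6 estimate of 2.77 (SE 0.95), against a true value of 2.70.

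**5. Effect on the margin.** Section 2.10 assumes that PWS has the same effect as YGJ. The expected lower 95% limit from Hypothesis 2 is then 2.70 − 1.96 × 0.953 = 0.83 from a week-6 contrast. From the additive model over four visits at ρ = 0.5 it is 2.70 − 1.96 × 0.75 = 1.23 if the effect is constant. It is 1.35 − 1.96 × 0.75 = −0.12 under the first pattern. The model wording thus moves the margin as well.

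**The case against.** The strongest defence is that the target is not in doubt. Week 6 appears in the sample size, the primary outcome and every hypothesis. The method is named as an MMRM, which commonly includes group-by-visit. Articles often list factors without writing out interactions, and an analyst bound by the hypotheses would have to produce a week-6 contrast. A full protocol or analysis plan, not shown, may say so.

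This has weight as a forecast of what will be done, but it does not repair the text. The article goes beyond naming a method: it lists the random and fixed factors, and those listed do not yield the stated parameter. The last paragraph of section 2.11 also gives differences in trend across visits to a separate repeated-measures analysis of variance, which fits a primary model without the interaction.

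Three stronger readings are tempting, and the documents do not support them.

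- A reader might infer that the model averages weeks 3, 6, 9 and 24. No section says so. Section 2.12 points away from week 24, while the measurement schedule alone leaves even week 0 possible.
- A reader might infer that power must fall. That depends on an assumed time course. If the effect is constant, pooling raises power.
- A reader might fault the absence of a covariance structure, a degrees-of-freedom method or a baseline-by-visit term. These are ordinary analysis-plan detail and no error in an article.

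In addition, equal visit weights hold only for complete data. With the planned 20% dropout the pooled effect would be a precision-weighted mean.

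**Conclusion.** The point stands as a mismatch between a stated model and a stated hypothesis. As listed, the model gives one group effect pooled over unnamed visits, whereas Hypotheses 1 to 3, the noninferiority margin and the planning difference of 2.70 concern week 6. The two agree only if the effect is constant over the modelled visits.

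The size cannot be fixed from the documents, which give no effect at other visits and no correlation. Under the assumptions above, the pooled effect over four visits ranges from 1.35 to the full 2.70, with power between 36% and about 95% against 81% for the week-6 contrast. Leaving out week 24 lessens the gap under the fading pattern (1.80) but does not close it. The direction of the power change is open; the mismatch in what is estimated does not depend on it. Nor do the documents show that the trial will in fact test the wrong quantity, only that the model sentence as written does not deliver the right one.

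**What to change.** In section 2.11, under Hypothesis 1:

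- add group-by-visit to the fixed effects;
- state which visits enter the model, in particular whether week 24 does, and whether baseline TDS is a response or a covariate;
- name the week-6 between-group contrast from that model as the test for Hypothesis 1;
- say that the week-6 contrasts from the same model serve Hypotheses 2 and 3, and that the week-6 interval for Hypothesis 2 supplies the margin.

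The sample size stays as it is, because 44 and 22 were already calculated for the week-6 difference. The cost is a change of wording, a few degrees of freedom, and the precision that pooling would have given if the effect were truly constant (four-visit SE 0.75 to 0.84 against 0.95 at week 6, under the assumed correlations).

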**Hypothesis** **2.**
*[*

$H_{0}\;:\;\mu_{3}=\mu_{2},\;H_{1}\;:\;\mu_{3}\neq \mu_{2}$

*]*

*-*

$\mu_{2}$

*: Change in TDS score of the usual care group at week 6*

*-*

$\mu_{3}$

*: Change in TDS score of the PWS group at week 6*

**Hypothesis** **3.**
*[*

$H_{0}\;:\;\mu_{3}-\mu_{1}>M,\;H_{1}\;:\;\mu_{3}-\mu_{1}\;\leq M$

*]*

*-*

$\mu_{1}$

*: Change in TDS score of the YGJ group at week 6*

*-*

$\mu_{3}$

*: Change in TDS score of the PWS group at week 6*

To evaluate the noninferiority of YGJ compared to PWS, Hypothesis 3 will be tested in the same way as Hypothesis 1. However, since the noninferiority test is a single test, the significance level will be set to 2.5%, and the noninferiority margin will be defined as the lower limit of the 95% CI of Hypothesis 2. The multiple test problem will be solved using the fixed sequence method [29]. In other words, if the statistical test result for Hypothesis 1 is significant, the test for Hypothesis 2 will be performed, and if the statistical test result for Hypothesis 1 is not significant, the test for Hypothesis 2 and Hypothesis 3 will not be performed. If the statistical test result for Hypothesis 1 is significant and the test for Hypothesis 2 is performed, and if the statistical test result for Hypothesis 2 is significant, the test for Hypothesis 3 will be performed. If the statistical test result is not significant, the test for Hypothesis 3 will not be performed. If possible, subgroup analysis will be performed by categorizing the participants’ baseline characteristics, including age (65 years old or older/under), Rome IV subtype (EPS, PDS, and overlap), type of FD pattern identification (according to the standard tool for pattern identification of FD [21]: spleen–stomach deficiency and cold, spleen deficiency with qi stagnation, liver–stomach disharmony, cold–heat complex, spleen–stomach dampness and heat, and dietary retention and stagnation), deficiency and excess pattern identification, and the presence or absence of *Helicobacter pylori* infection and spleen qi deficiency syndrome (cut off score: 43.18 points in SQDQ [27]). In addition, we will combine the results of the YGJ and PWS groups corresponding to herbal medicine and compare them with the usual care control group.

Other secondary outcome measures will be tested in the same way as the primary outcome measure. In addition, to compare the difference between the values before and after treatment in each group, the continuous variable will be analyzed using Student’s paired *t*-test or Wilcoxon signed-rank test, and the discrete variable will be Fisher’s exact test. Repeated measures analysis of variance will be performed to compare the differences in trend change in each group of visits, and Dunnett’s procedure (based on the baseline) will be used as a multiple comparison correction.

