### 2.10. Sample Size Calculation

The primary objective of this study is to compare and evaluate the effectiveness of 6 weeks of administration of YGJ compared to usual care in participants with FD. We will test whether there is a difference in the degree of reduction in TDS scores between the two groups after 6 weeks through a superiority test. Based on the results of a previous study comparing YGJ and a placebo [19], and considering the 15% placebo effect, it is assumed that the difference between the average TDS change between the YGJ and usual care groups after 6 weeks is 2.70, and the standard deviation is 3.65. The significance level is 0.05, and the power is 80%. Taking into account the previous studies [11,19] and ethical issues, the ratio between the YGJ and usual care groups is assigned at 2:1. Therefore, 44 and 22 participants are required for the YGJ and usual care groups, respectively.

Additionally, the second purpose of this study is to evaluate the noninferiority of YGJ compared with that of PWS. For this, the noninferiority margin should be defined based on the results of the effect evaluation between the PWS and usual care groups. However, due to the lack of prior research and related data, we will first test the superiority of PWS compared to usual care after 6 weeks to define the noninferiority margin. Under the assumption that the effect size of the YGJ and PWS is the same, 44 participants are also required in the PWS group. Therefore, considering the 20% dropout rate, a total of 140 participants, including 56, 56, and 28 participants in the YGJ, PWS, and usual care groups, respectively, are required.

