## 3. Discussion

The present study is a protocol for a randomized, assessor-blind, multicenter, controlled clinical trial evaluating the effectiveness and safety of YGJ compared with usual care and PWS in patients with FD, and will be conducted in conjunction with a cost-effectiveness analysis. We aim to test the superiority of YGJ to usual care and noninferiority to PWS for the treatment of FD. In addition, although YGJ is actively used in the Korean medicine clinical field for the treatment of FD, a cost-effectiveness analysis has not yet been conducted for this. We intend to prepare the basic data for health insurance benefit registration of YGJ by confirming the cost-effectiveness of YGJ compared to PWS, the most commonly used health insurance benefiting herbal medicine for the treatment of FD in Korean medicine clinical settings [7]. Based on consultation with Korean medicine gastroenterology experts and prior literature that stated that at least 4–6 weeks of treatment was required to see the significant therapeutic effect of YGJ, we set 6 weeks as the administration period of investigational products [12].

According to the guideline recommendations for outcome measures used in clinical trials for FD [32], the primary efficacy outcome measures to be used in FD clinical trials are diverse and have not yet been standardized. Additionally, in Korea, a patient-reported outcome measure that has been verified as recommended by local or global guidance has not yet been developed. Accordingly, it is recommended to use the total symptom score and OTE as the primary efficacy endpoint for FD clinical trials [32]. Therefore, in our study, the TDS score, which was used frequently as the primary outcome measure in previous studies on FD [11,19,22], was selected as the primary outcome according to the expert consensus, and OTE was set as the secondary outcome. Additionally, based on such previous studies [11,19], a sample size suitable for hypothesis testing was calculated in the present study.

In addition, based on previous studies showing that psychological factors are closely related to the pathogenesis of FD [12,33,34], we will measure HADS as a secondary outcome to determine whether anxiety and depressive symptoms are improved after administration of investigational products and to examine the correlation with other outcomes such as TDS and ghrelin.

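### The noninferiority margin is taken from the trial's own PWS versus usual care interval, so the PWS mean cancels and Hypothesis 3 does not compare YGJ with PWS

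*Protocol article*

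**What the plan says.** Section 2.10 names noninferiority of YGJ to PWS as the second purpose of the trial and explains where the margin comes from: "due to the lack of prior research and related data, we will first test the superiority of PWS compared to usual care after 6 weeks". Section 2.11 repeats this and then fixes the rule under Hypothesis 3: "the noninferiority margin will be defined as the lower limit of the 95% CI of Hypothesis 2". With mu1 for YGJ and mu3 for PWS, the alternative is that mu3 - mu1 is no larger than M, tested one-sided at 2.5%. The tests run in fixed sequence. Hypothesis 1 (YGJ versus usual care) comes first and then Hypothesis 2 (PWS versus usual care), and "if the statistical test result for Hypothesis 2 is significant, the test for Hypothesis 3 will be performed". The Discussion restates the aim: "We aim to test the superiority of YGJ to usual care and noninferiority to PWS for the treatment of FD".

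The document gives no numerical margin and no fraction of the PWS effect to be preserved. It makes no allowance for M being estimated from the same PWS participants who enter the noninferiority comparison. The sample size is derived for the two superiority comparisons only.

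**The concern.** A noninferiority margin should limit how much worse YGJ may be than PWS. Here the limit moves with the PWS result: the better PWS does, the larger the permitted loss, point for point. The margin also equals the whole lower bound of the PWS effect, so none of that effect has to be retained. Because M is random and correlated with the estimate it is compared with, the nominal 2.5% does not refer to any fixed null hypothesis about YGJ and PWS.

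The Introduction ties noninferiority to a possible insurance listing of YGJ. If the test does not respond to how well PWS works, neither a positive nor a negative result supports a statement about YGJ relative to PWS.

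**Working it through.** **Inputs.** From section 2.10: assumed difference 2.70 for YGJ versus usual care, SD 3.65, two-sided 5%, 80% power, ratio 2:1, PWS effect assumed equal to YGJ, 44/44/22 (YGJ/PWS/usual care) evaluable, and 56/56/28 after 20% dropout. Both sets of sizes are used below, because the full analysis set in section 2.11 may keep more than the 44/44/22 completers.

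**The plan's own figure reproduces.** Usual care n = 1.5 × [3.65 × (1.960 + 0.842) / 2.70]² = 21.5, rounded to 22, hence 44 for YGJ. Then 22 / 0.8 = 27.5, rounded to 28, and 2 × 28 = 56 per herbal arm, 140 in total.

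**The decision rule.** Let x1, x2, x3 be the estimated week 6 reductions for YGJ, usual care and PWS.

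- Margin: M = (x3 - x2) - 1.96 × SE32
- Noninferiority: (x3 - x1) + 1.96 × SE31 ≤ M
- Subtract x3 from both sides: x1 - x2 ≥ 1.96 × (SE31 + SE32)

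**The bar with the planned numbers.**

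- 44/44/22: SE31 = 3.65 × √(2/44) = 0.778 and SE32 = 3.65 × √(1/44 + 1/22) = 0.953. Bar = 1.96 × 1.731 = 3.39. Hypothesis 1 needs 1.96 × 0.953 = 1.87.
- 56/56/28: SE31 = 0.690 and SE32 = 0.845. Bar = 3.01. Hypothesis 1 needs 1.66.

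The standard error of x1 - x2 equals SE32, because the herbal arms have equal size. With a true YGJ effect of 2.70, the chance of clearing the bar is Φ((2.70 - 3.39)/0.953) = 23% with 44/44/22 and Φ((2.70 - 3.01)/0.845) = 36% with 56/56/28. The PWS effect does not enter.

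**Probability that all three tests succeed.** Simulated with normal data, pooled SD and t critical values. Effects are true reductions relative to usual care.

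| YGJ effect | PWS effect | 44/44/22 | 56/56/28 |
|---|---|---|---|
| 2.70 | 2.00 | 21% | 32% |
| 2.70 | 2.70 | 23% | 35% |
| 2.70 | 5.40 | 23% | 35% |
| 1.35 | 2.70 | 1.7% | 2.6% |
| 2.0 | 4.0 | 7% | 12% |
| 4.0 | 4.0 | 72% | 87% |
| 4.0 | 6.0 | 72% | 87% |
| 5.0 | 10.0 | 95% | 99% |

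With YGJ 4 and PWS 6 (44/44/22), about 48% of trials would declare YGJ noninferior while the same data show PWS significantly better at two-sided 5%.

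**A retention contrast for comparison.** Take H0: (mu1 - mu2) ≤ 0.5 × (mu3 - mu2). With 44/44/22 its SE is 3.65 × √(1/44 + 0.25/44 + 0.25/22) = 0.728. At the boundary cases 2.70/5.40 and 5/10 the simulated false claim rate is 2.5%. With both effects at 2.70, power is Φ(1.35/0.728 - 1.96) = 46% alone and 39% through the sequence.

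**The case against.** Several limits on the point are fair.

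- **PWS is not wholly absent.** It must beat usual care before Hypothesis 3 is tested, and its variance and sample size enter the bar. But that gate compares PWS with usual care, and a stronger PWS only makes it easier to pass.
- **The cancellation is exact only if one model supplies both contrasts.** The protocol does not say whether the repeated-measures model is fitted jointly or pairwise. Separate fits, or different covariates, would make it approximate, with the same behaviour.
- **Under the planning assumptions, false claims are not the main harm.** If PWS has the planned 2.70 and YGJ half of it, the false claim rate is 1.7% to 2.6%. Inflation needs a PWS effect above plan. The 5/10 case is extreme on a scale with maximum 8 × 3 = 24. At the planned effects the visible consequence is low power.
- **Missing a claim when YGJ is truly better is not peculiar to this rule.** With 44/44/22, the 50% retention contrast also fails in about 62% of trials at YGJ 2.70, PWS 2.00.
- **The direction of change can be inferred.** Section 2.10 speaks of reduction, and the improvement formula in section 2.9.2 is baseline minus week N. The unstated sign under the hypotheses is a wording matter.
- **Prior data were lacking.** That explains why there is no historical margin. It does not justify one computed from the same PWS data, and a three-arm retention test needs none.

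These points narrow the consequences and leave the defect in place.

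**Conclusion.** The concern holds and should be corrected before analysis. As written, Hypothesis 3 is a stricter repeat of Hypothesis 1, with a bar of 3.39 points (3.01 with 56/56/28) instead of 1.87 (1.66). It gives no control over declaring YGJ noninferior when it is materially worse than PWS. At the planned effects it succeeds in 23% of trials (35% with 56/56/28), and equally often when PWS is twice as effective as YGJ. False claims exceed 2.5% mainly when PWS does better than the assumed 2.70.

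These figures rest on SD 3.65 in every arm, normal estimates, M read as the observed confidence limit, and both contrasts taken from the same week 6 estimates. Treating half the PWS effect as the boundary of a false claim is an assumption of this review; the protocol states none. Hypothesis 1, the primary objective, is tested first and is unaffected.

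**What to change.** Replace the data-derived margin with a rule fixed before any comparative week 6 data are examined.

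- **Preferred: retention of effect.** Test H0: (mu1 - mu2) ≤ theta × (mu3 - mu2), one-sided at 2.5%, as a single linear contrast of the week 6 least-squares means from one three-arm model, with theta stated and justified. The 0.5 used above is illustrative.
- **Alternative: a fixed margin in TDS points with a clinical justification.** Half of the assumed 2.70 is 1.35, again only an illustration. For 80% power at no true difference it needs 2 × [3.65 × 2.802/1.35]² = 115 evaluable per herbal arm. With 44 per arm, power is 41% alone and 28% through the sequence.

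Keep the order Hypothesis 1, 2, 3. State that change means baseline minus week 6, so that the inequality and the interval limit point the intended way; under the opposite sign both would reverse.

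The cost is wording, a justification of the fraction or margin, and an open statement of power. No new participants or data are needed to correct the rule. If the sponsor finds the resulting power too low and will not enlarge the herbal arms, the YGJ versus PWS comparison should be presented as an estimate with a confidence interval, without a noninferiority claim.
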